**Data processing Procedure**

- - Questionnaires will be visually scanned soon after the interview and marked for omissions, inconsistencies, or mistakes that will be addressed immediately
  - SPSS will be used and data will be entered after creating a template for each data entry file with appropriate logical and consistency checks
  - Data will be continuously entered as the data are being generated in the hospital
  - Data will be validated by a series of logical and range checks, producing summary statistics and tables
  - Data will be immediately copied on the hard disks of two computers as soon as data verification will be completed

**Safety Plan**

Gastrointestinal symptoms (Nausea, Vomiting, Diarrhea and Fever) are the most likely adverse event. The safety population will include all subjects who received at least one dose of the investigational products under study. Descriptive statistics will be used to summarize adverse events, safety results, and demographic variables. Reasons for dropouts and timing will be documented. Any dosing errors will be described, with any adverse events resulting.

## Data Analysis

Data will be entered into the pre-tested case record forms(CRFs) using SPSS (20.0 version, Armonk, NY) and finally cleaned with a repeated check. Data will be presented using frequency with percentage for categorical variables. Mean with standard deviation will be used for symmetrical continuous variables. Median with interquartile range will be used for asymmetrical numeric variables. To know the outcome of the intervention in our study children bivariate, crude analyses of the association will be done that will involve Chi-square or Fisher’s exact test for comparing differences in proportion and t-tests for numeric variables between the groups. Nnonparametric continuous data will be analyzed by Mann-Whitney U-test. Results from all children will be included in the analysis of the study on an intention-to-treat basis. Data from children withdrawn because of failure to respond, or voluntary dropouts will be included in the analysis up to the time of withdrawal. A supplementary analysis excluding the children withdrawn may also be done. A probability of less than 0.05 will be considered statistically significant.

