**Biological sample collection**

We will collect blood, stool and urine from the participants at enrolment and at the end of nutrition intervention. Overall, 5 ml of whole venous blood will be collected aseptically from each of the participants as per the SOPs. The blood biomarkers that will be tested in this study are L-carnitine, Citrulline, KT Ratio, C-reactive protein (CRP), and Alpha-1-acid glycoprotein (AGP). CRP is an acute phase protein and can be detected during infection. Increased level of AGP in serum indicates systemic tissue injury, inflammation and infection. Both Citrulline and KT Ratio indicate EED in children. Stool will be collected to investigate the concentrations of MPO, NEO and A1AT in the fecal samples. We will measure L-carnitine levels in the urine samples of each participants. All the assays will be done at icddr,b.

Laboratory Investigation

| **Investigations** | **Type of tests** |
| --- | --- |
| L carnitine in plasma and urine | Enzyme-linked immunosorbent assay (ELISA)* |
| Myeloperoxidase (MPO) | Enzyme-linked immunosorbent assay (ELISA)* |
| Neopterin (NEO) |
| Alpha-1 antitrypsin (AAT) |
| Citrulline |
| Kynurenine: Tryptophan (KT) Ratio |
| C-reactive protein (CRP) |
| Alpha-1 acid glycoprotein (AGP) |
| Serum creatinine (S. Cr) | icddr,b diagnostic laboratory |
| Potential Renal Solute Load (PRSL) |

*ELISA will be done at icddr,b laboratory

Outcome measures/variable:

Primary Outcome Variable:

1. Rate of weight gain

Secondary Outcome Variable:

1. Duration of hospital stays
2. EED biomarkers (MPO, NEO, A1AT, KT Ratio, Citrulline)

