### Detailed Comments

Please briefly provide your opinions of this proposal, giving special attention to the originality and feasibility of the project, its potential for providing new knowledge and the justification of financial support sought; include suggestions for modifications (scientific or financial) where you feel they are justified. (Use additional pages if necessary)

**Title:** Role of L-Carnitine supplementation on rate of weight gain and biomarkers of Environmental Enteric Dysfunction (EED) in children with severe acute malnutrition

**PI:** [name]

**Reviewer**: [name]

[name] and colleagues are seeking to fill a crucial knowledge gap in the field of malnutrition and EED by performing a clinical trial of Levocarnitine for the treatment of severe acute malnutrition and EED. The trial is a well-designed randomized placebo-controlled double blinded trial. In addition block randomization will be used which may help to decrease bias given the smaller sample size. There is sufficient background data to suggest Levocarnitine’s utility in treating EED and malnutrition and thus, such a trial is scientifically warranted. The biomarkers of EED selected are broad, encompassing enteric inflammation, systemic inflammation, and intestinal integrity. The analysis plan is reasonable although authors should clearly state an adjusted model will also be created and describe the covariates included (or how they will be selected). The intervention is relatively benign when taken PO. The safety plan seems adequate for this small trial given the side effect profile of the intervention (i.e. generally do not see the cardiac effects when given PO).

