Investigators plan to use a standard dose of 100mg/kg/day. However, literature supports titration to higher doses in certain children. It is unknown exactly how deficient children with SAM and EED are and thus it may be that this dose is insufficient to replete some children. Correction for baseline carnitine levels may be indicated in the final analysis but understanding the distribution of those baseline levels will also be a valuable addition to our current knowledge. In terms of the secondary outcome of study of Levocarnitine’s effect on EED, the interval of 15 days may be too short to recognize an effect on certain biomarkers. Specifically, those of gut permeability may take longer to correct. Also, the degree of baseline elevation in inflammatory biomarkers (including enteric inflammation) may be dependent on the type of pathogen causing the diarrhea that led to the child’s admission. Children with secretory diarrhea will have less elevation than those with inflammatory pathogens such as Campylobacter or Shigella. Inflammatory biomarkers to these pathogens may decrease regardless of intervention as the infection clears although likely will not normalize. One way to create a more heterogenous group without expensive pathogen testing would be to exclude children with fecal RBC positivity. Although pathogens such as Campylobacter are increasingly being recognized causing non-bloody diarrhea in addition to the more classic bloody diarrhea, this may help in excluding children with the highest levels of colitis (i.e. those that would lead to fecal RBC testing being positive). Alternatively, if the budget allows, fecal pathogen testing could be arranged and only children with viral disease enrolled as it would be expected that viral pathogens change the inflammatory biomarkers to a lesser degree. Of course, co-pathogen carriage may make screening difficult. Finally, there is evidence that the enteric microbiota plays an important role in carnitine metabolism. While likely beyond the scope of this project and budget, it would be reasonable to bank a separate aliquot of stool for the purpose of future microbiome studies. If this trial does demonstrate an effect in the treatment group, external funding for this line of question could potentially be secured. This should be a separate aliquot to limit freeze-thaw cycles and be stored in RNase/DNase free cryovials at -80oC.

Response to External Reviewer’s comments:

Reviewer: [name]

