Comment: “[name] and colleagues are seeking to fill a crucial knowledge gap in the field of malnutrition and EED by performing a clinical trial of Levocarnitine for the treatment of severe acute malnutrition and EED. The trial is a well-designed randomized placebo-controlled double blinded trial. In addition, block randomization will be used which may help to decrease bias given the smaller sample size. There is sufficient background data to suggest Levocarnitine’s utility in treating EED and malnutrition and thus, such a trial is scientifically warranted. The biomarkers of EED selected are broad, encompassing enteric inflammation, systemic inflammation, and intestinal integrity. The analysis plan is reasonable although authors should clearly state an adjusted model will also be created and describe the covariates included (or how they will be selected). The intervention is relatively benign when taken PO. The safety plan seems adequate for this small trial given the side effect profile of the intervention (i.e. generally do not see the cardiac effects when given PO).”

Response: Thank you very much for your comments and considerations.

Comment: “Investigators plan to use a standard dose of 100mg/kg/day. However, literature supports titration to higher doses in certain children.”

Response: Thank you so much for your opinion. We agree with you regarding evidence on titration. However, slow administration of the dose is also evident. Therefore, we will give the supplementation of oral solution slowly to our study participant as per guidance of published literature.

Comment: “It is unknown exactly how deficient children with SAM and EED are and thus it may be that this dose is insufficient to replete some children.”

Response: Dear reviewer, thank you for your valuable suggestion. In previous study on carnitine supplementation in SAM children they gave supplementation of 100 mg/kg/day and found significant weight gain in SAM children. Several studies also showed that supplementation of 50-150 mg/kg/day in 3-4 divided doses was effective in increasing the rate of weight gain. Therefore, we have designed our study to give 100mg/kg/day in 3 divided doses. We think it will be sufficient to replete the deficiency (5, 26).

Comment: “Correction for baseline carnitine levels may be indicated in the final analysis but understanding the distribution of those baseline levels will also be a valuable addition to our current knowledge.”

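### The efficacy analysis names only crude two-group tests, leaving unused the baseline values the trial collects; the cost is precision, chiefly for the five EED biomarkers

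*Protocol*

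**What the plan says.** Data Analysis is the only efficacy analysis text in the protocol. It says that "bivariate, crude analyses of the association will be done", with chi-square or Fisher's exact test for proportions and "t-tests for numeric variables between the groups". Where the data are not suited to a t-test, "continuous data will be analyzed by Mann-Whitney U-test". No regression model, covariate or stratification factor appears. The one further analysis is optional and leaves out withdrawn children.

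The baseline data exist. Under Biological sample collection, "We will collect blood, stool and urine from the participants at enrolment and at the end of nutrition intervention". Anthropometric measurements has weight, length and MUAC taken at enrolment and daily. Investigations has plasma carnitine measured before and after supplementation in every child.

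In Appendix 1, External Reviewer 1 called the analysis plan reasonable but wrote that "authors should clearly state an adjusted model will also be created and describe the covariates included". The reply to that comment was "Thank you very much for your comments and considerations". The same reviewer also wrote "Correction for baseline carnitine levels may be indicated in the final analysis". The investigators answered that they would look at the distribution of baseline carnitine, and promised no adjustment.

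Randomization gives two schemes joined by the word *Or*. The table in the first (Figure 3) lays out blocks by sex and by type of SAM (WLZ/MUAC criterion or oedema). The second uses permuted blocks of varying size and mentions no strata.

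**The concern.** With 49 children per arm, and faecal and blood markers that may vary widely between children, the arms can differ at baseline by chance. A crude comparison neither corrects such a difference nor removes the part of the outcome variance that baseline explains.

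The gap is widest for MPO, NEO, A1AT, KT ratio and citrulline. Each is measured twice, but Data Analysis does not say whether the test is applied to the end-of-intervention value or to the change. These two analyses have different precision and can give different answers, so the choice should not be open once the data are seen.

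The point was also raised before approval. A request for an adjusted model sits in the protocol's own appendix, and the analysis text does not act on it.

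**Working it through.** **1. The plan's own figure.** Inputs from Sample Size Calculation: SD 4.3, difference 2.4, margin 0.1, Z 1.645 and 0.845, attrition 10%. The fraction in the printed formula is not shown. Reading it with 2.4 − 0.1 = 2.3 in the denominator:

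n = 2 × ((1.645 + 0.845)/2.3)² × 4.3² = 43.3, so 44; 44/0.90 = 48.9, so 49 per group.

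This reproduces the stated 49. It assumes an unadjusted comparison, with about 44 evaluable children per arm.

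**2. What adjustment does to the variance.** In a linear model with baseline covariates, the residual variance is the outcome variance times (1 − r²), where r is the (multiple) correlation of the outcome with those covariates. r is not in the documents, so a range is shown.

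| r | 1 − r² | Equivalent extra children, 1/(1 − r²) − 1 |
|---|---|---|
| 0.2 | 0.96 | 4% |
| 0.3 | 0.91 | 10% |
| 0.5 | 0.75 | 33% |
| 0.6 | 0.64 | 56% |

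**3. Why end value or change matters for the biomarkers.** Assume equal variance before and after. Relative to a crude comparison of end values (factor 1), a comparison of changes has variance factor 2(1 − r), and the baseline-adjusted model has 1 − r².

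- r = 0.3: change 1.40, adjusted 0.91.
- r = 0.5: change 1.00, adjusted 0.75.
- r = 0.6: change 0.80, adjusted 0.64.

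The two unadjusted options change order at r = 0.5. The adjusted model is the most precise of the three at each r shown.

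**4. Primary outcome, illustrative power.** Two-sided 0.05, 44 per arm, difference 2.4, residual SD = 4.3 × √(1 − r²), noncentral t distribution. Noncentrality = 2.4/(SD × √(2/44)).

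| r | Residual SD | Noncentrality | Power |
|---|---|---|---|
| 0 | 4.30 | 2.62 | 73.5% |
| 0.1 | 4.28 | 2.63 | 73.9% |
| 0.2 | 4.21 | 2.67 | 75.2% |
| 0.3 | 4.10 | 2.74 | 77.4% |
| 0.4 | 3.94 | 2.86 | 80.6% |
| 0.5 | 3.72 | 3.02 | 84.8% |

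On the protocol's own basis (one-sided, difference 2.3), unadjusted power is about 80%. The 73.5% starting value therefore reflects the two-sided test and is not a result of leaving out covariates.

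**5. Ignoring strata, if there are any.** A simulation used four balanced strata, 11 children per arm in each, no treatment effect and 20,000 runs. The type I error of the plain t-test was 5.2%, 3.9%, 2.9% and 2.0% when strata explained 0%, 10%, 20% and 30% of the outcome variance. The crude test becomes conservative and does not produce excess false positives.

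**The case against.** The strongest reply is that this is a preference for efficiency and not an error. Unadjusted t-tests and Mann-Whitney tests are valid in a randomised trial, and step 5 shows that ignoring prognostic strata errs on the safe side. That stands: no bias is alleged. A second reply is that covariate lists commonly belong in the statistical analysis plan, which is not shown. This has some force, and Data Analysis does not expressly exclude adjustment. But the section makes a positive choice of crude tests, so an adjusted primary analysis elsewhere would depart from it.

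Three stronger readings are tempting and are not supported.

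- A reader might infer that baseline is ignored altogether. For the primary outcome this is wrong: the rate of weight gain is derived from weight at enrolment. Baseline is only absent as a covariate.
- A reader might infer that the trial is stratified by sex and oedema and that the analysis ignores known strata. Those factors appear only in the table of the first randomisation scheme. If the second is used, there are no stated strata to adjust for.
- A reader might infer that the investigators brushed aside every comment on adjustment. The request for an adjusted model drew only thanks, but the carnitine remark got a reply about examining its distribution. The external reviewer also asked for an adjusted model as an addition, not as a replacement.

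The gain may also be small: at r of 0.2 or less it is under two percentage points of power for the primary outcome.

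**Conclusion.** The point holds as one about precision and prespecification. The stated efficacy analysis is crude throughout, uses no baseline covariate or randomisation factor, and does not say how the paired biomarker measurements enter the comparison. The tests are valid, so what is at stake is wasted information and uncorrected chance imbalance in a trial of 98 children.

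The case is strongest for the five EED biomarkers, where an assumed r of 0.3 to 0.6 would cut the variance by 9% to 36% relative to comparing end values. For weight gain, power would rise from 73.5% to between 75.2% (r = 0.2) and 84.8% (r = 0.5). All of these gains rest on an assumed r and are illustrative. The part about strata depends on which randomisation scheme is used.

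**What to change.** Amend Data Analysis before unblinding.

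- **EED biomarkers:** for each, a linear model of the log day-15 value on arm and log baseline value (untransformed if not skewed). For log models, report the ratio of geometric means with a 95% confidence interval. This also settles the choice between end value and change.
- **Primary outcome:** a linear model of weight-gain rate on arm with a short, named list of baseline covariates, for example WLZ and age, plus the factors actually used to stratify randomisation. First reconcile the two schemes under Randomization, and include sex and type of SAM only if the scheme in the Figure 3 table is the one used.
- **Crude tests:** keep them as supportive.
- **Baseline carnitine:** label any analysis that uses it as exploratory.

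The cost is wording only. The variables named are collected or follow from measurements already planned, and no change to sample size or visits is needed.

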**Management**

Children will be given their first dose of supplementation when they would be considered improved, i.e. no diarrhea for last 24 hours, patient fulfill the criteria of NRU transfer (presence of oedema, or/and WLZ <-3SD, or/and WAZ <-4SD). At NRU after randomization trained research staff will observe each child for 60 minutes following ingestion of investigational product and record any adverse event- nausea, vomiting etc. Vomiting is defined as the forceful emptying of stomach contents and will be recorded if it happened within 60 minutes following the administration of investigational product. Children will get supplementation of investigational product in addition to standard of care at NRU for 15 days. Supplementation will be given at every 8 hours under supervision of a trained staff.

**Study Days**Patients will be followed up every day by a study physician at NRU for 15 days. Adverse events will be documented and drug accountability recorded. During this intervention period if study participants fulfill the discharge criteria of NRU (WLZ/WHZ ≥ -2SD, WAZ ≥ -3SD and oedema resolved), we will discharge the patient with remaining dose of the syrup and advise them to come for follow up into after completion of the remaining dose. This same method will be applicable for both the intervention arm and placebo arm.

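### Counting withdrawn children only up to withdrawal, with t-test or Mann-Whitney, makes an early failure look like a short hospital stay; the arms' comparison is biased if early withdrawal differs between them

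*Protocol*

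**What the plan says.** The outcome list in the protocol names "Duration of hospital stays" as a secondary outcome, and it is also a specific objective. The study-days text under Management explains how a stay ends: "During this intervention period if study participants fulfill the discharge criteria of NRU", the child goes home with the remaining syrup. In its 30 June 2021 reply to the Research Review Committee, the investigator describes first dosing on NRU day 1 and discharge on these criteria, and says that this is how the effect on hospital stay will be estimated. The intended quantity is therefore a time to recovery.

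The Data Analysis section sets the rules for all outcomes together:

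- Analysis set: "Results from all children will be included in the analysis of the study on an intention-to-treat basis".
- Withdrawn children: "Data from children withdrawn because of failure to respond, or voluntary dropouts will be included in the analysis up to the time of withdrawal".
- Tests: "t-tests for numeric variables between the groups", and for skewed data, "continuous data will be analyzed by Mann-Whitney U-test".
- Alternative: "A supplementary analysis excluding the children withdrawn may also be done".

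Nothing exempts hospital stay from these rules, censors it at withdrawal, or gives a withdrawn child an unfavourable value.

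**The concern.** For a duration, the data up to withdrawal are simply the number of days until withdrawal. A t-test or rank test takes that number as a finished stay. A child withdrawn early for not responding then ranks as better than a child who recovered and was discharged later. This is a stated rule, not a detail left open for a later analysis plan.

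Early departure is foreseen. The sample size allows 10% attrition, and the reply to the first external reviewer says that most caregivers would not let a child stay for about 30 days. The optional supplementary analysis does not help, because it removes the failures instead of scoring them. At stake is the direction of a secondary result: an arm with more early failures could appear to shorten hospital stay.

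**Working it through.** **Inputs from the protocol.** There are 49 children per arm and 10% attrition, so 0.10 × 49 = 4.9, about five children per arm. The stated size reproduces if the formula's missing fraction has δ − δ₀ as its denominator: 2 × ((1.645 + 0.845)/(2.4 − 0.1))² × 4.3² = 43.3, rounded up to 44, and 44/0.90 = 48.9, rounded up to 49. That calculation concerns weight gain. The protocol gives no mean, SD or withdrawal pattern for hospital stay, so every stay and withdrawal input below is an assumption.

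**Direction, by arithmetic.** Let recovered children stay 15 days, let failures truly need 25 days, and let 8 v 2 of 49 be withdrawn.

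- True mean difference: (8 − 2) × (25 − 15)/49 = +1.22 days, worse for the arm with more failures.
- Recorded difference if withdrawal is on day w: (8 − 2) × (w − 15)/49.
- Day 5 gives −1.22, day 10 gives −0.61, day 15 gives 0.00 and day 20 gives +0.61.

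The recorded difference is always shifted towards the arm with more failures. The sign reverses only when withdrawal comes before the typical discharge day. With 5 v 5 withdrawn at the same times, the recorded and true differences are both zero.

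**Size, by simulation.** Assume no true effect on stay, 49 per arm, a gamma-distributed stay with mean 14 days and SD 5.7, and withdrawal uniform on days 2 to 8 (mean 5). The expected mean difference is (difference in withdrawal share) × (5 − 14). Rejection is by two-sided Mann-Whitney at 0.05, with 8,000 simulated trials per row.

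| Withdrawn, arm 1 v arm 2 | Mean difference (days) | Rejection rate |
|---|---|---|
| 10% v 10% | 0 | 5% |
| 12% v 8% | 0.04 × (−9) = −0.36 | 6% |
| 14% v 6% | 0.08 × (−9) = −0.72 | 10% |
| 15% v 5% | 0.10 × (−9) = −0.90 | 12% |
| 20% v 10% | 0.10 × (−9) = −0.90 | 12% |
| 20% v 5% | 0.15 × (−9) = −1.35 | 22% (21% to 23% in repeat runs) |

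The first four rows average to the planned 10% attrition. The t-test is affected similarly.

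**Later withdrawal.** If withdrawal is on days 8 to 15 (mean 11.5), the shift is 0.10 × (11.5 − 14) = −0.25 day for 20% v 10%, and 0.15 × (−2.5) = −0.38 day for 20% v 5%. The rejection rate is then about 6% for both, and no repeat run exceeded 8%.

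**The case against.** The strongest reply is that the protocol never says how hospital stay is scored for a withdrawn child. The rule is general, and daily weights are its natural object. Withdrawal from the study is also not discharge: the ethics section promises unbroken hospital care to those who refuse and lets families withdraw at any time, so a child withdrawn on day 4 may stay on the ward. This stands as a limit, since the four-day score is what the rule yields when applied to stay, not something the protocol spells out. It does not remove the problem. If the true stay can be observed, cutting it at withdrawal discards it, which sits badly with the intention-to-treat sentence.

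It is also fair that the bias needs unequal early withdrawal. The only attrition figure is a single 10%, and a marked excess of non-response in one arm of a blinded placebo trial would suggest real harm rather than a clean null. In that case the error is worse in kind, because the harmed arm looks better, but calling it a false-positive rate is then loose.

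Three stronger readings are tempting, and the documents do not support them:

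- *A spurious stay result would by itself lead to L-carnitine being recommended.* The Potential Impact section asks for better weight gain and an effect on biomarkers of environmental enteric dysfunction as well as on stay.
- *The rule scores a death as a short stay.* It names only failure to respond and voluntary dropout; how death is handled is not stated there.
- *Pre-randomisation acute-phase days distort the comparison.* The reply to the Research Review Committee ties the outcome to NRU day 1. Even if stay were counted from admission, randomisation means that those days would add noise rather than favour an arm.

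**Conclusion.** The concern holds in conditional form. As written, the rule and the named tests treat an incomplete stay as a complete one, and the optional exclusion analysis is no repair. Arm means are understated whenever a child is withdrawn before recovery. The between-arm comparison is biased only when the number or timing of withdrawals differs by arm, and then always towards the arm with more failures.

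Under the assumed inputs, the false-positive rate ranges from nominal (equal withdrawal) through 12% (a 10-point imbalance, early) to about 22% (a 15-point imbalance, early). It is near nominal when withdrawal comes close to the usual discharge day. These figures illustrate size and do not predict this trial's error rate. The outcome is secondary and is one of three joint grounds for a recommendation, so this should be corrected but does not threaten the primary analysis.

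**What to change.** For hospital stay only, replace the up-to-withdrawal rule:

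- Define the outcome as time from randomisation (NRU day 1) to first meeting the protocol's existing discharge criteria.
- Keep recording this date for children who stop study treatment but remain in hospital, unless consent for data collection is withdrawn.
- Treat withdrawal for non-response that ends observation, leaving without meeting the criteria, and death as competing events that never count as discharge.
- Compare arms by cumulative incidence, with a sensitivity analysis that censors voluntary dropouts.
- Report each type of event by arm beside the result.

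The cost is a slightly more complex analysis and one recorded date (criteria met). The Safety Plan already requires reasons for and timing of dropout to be documented. No dose, visit or clinical rule changes.
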